#### Power

Power was estimated based on a small effect size (Cohen's d) of .2, because there was no solid basis for an expected effect size, and followed power analysis based on LGCM of an artificial longitudinal treatment dataset [69]. This effect size equated to a difference in slope of .23 SD of the control group slope (set at 20% of initial status). Power here refers to the power to detect a difference between the treatment and control groups in terms of mean rate of decline and/or in the variance of the decline rate at an alpha level of .05. A total sample-size of 350 was required for power of .84. To detect an interaction effect of .40 (moderate size) between initial status and treatment slope in the treatment group, with a main effect of .2, required a sample-size ≌ 275. We aimed for an initial sample of 420, allowing for an attrition rate of approx. 17%, resulting in *N *= 350 at time 4, giving sufficient power to detect the primary effects.

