### Statistical Considerations

#### Analysis

Latent growth curve modelling (LGCM) will be the main analysis method used to assess the effect of the intervention. LGCM is an appropriate and rigorous methodology to employ for intervention studies that aim to alter a developmental trajectory and has greater power to detect an effect than models traditionally used in examining interventions, such as ANCOVA or repeated measures ANOVA [69].

Four equally-spaced testing time points were used in this study because, firstly, four time points are required to distinguish between different growth forms (e.g., linear, quadratic) and, secondly, four time points are estimated to give adequate power. The cognitive domains will be modelled as latent variables, providing the cognitive factors prove to be measuring the same construct across time, following the initial planned modelling of the tasks and cognitive factors on baseline data using confirmatory factor analysis (CFA). The main effect of the intervention on each cognitive domain will initially be assessed separately following Muthèn and Curran [69]. The main intervention effect can be tested by modelling the shape of the curve, for the time-points of a construct, for treatment and control groups separately. Both groups are constrained to the same normative growth trajectory, and the treatment slope added to the treatment group. Statistical significance of the mean of the treatment slope indicates a significant main treatment effect. Within this framework, further tests will also examine interaction effects, to determine whether the magnitude of the treatment effect varies as a function of initial cognitive status, and whether other factors, such as carriage of the ApoE-e4 allele, sex, or initial *n*-3 status, moderate the treatment effect. Similar analyses will be undertaken for well-being.

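### The stated power of .84 at a total of 350 covers a mean and/or variance difference; for the mean-slope test that decides the main effect, the stated inputs give about .58

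*Protocol article*

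**What the plan says.** In the protocol article, under Statistical Considerations, Power:

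- The starting effect: "Power was estimated based on a small effect size (Cohen's d) of .2".
- Its translation to the growth-model scale: "This effect size equated to a difference in slope of .23 SD of the control group slope". A bracket adds that something, apparently the slope variance, was fixed at a fifth of initial status.
- What power means here: a difference between arms "in terms of mean rate of decline and/or in the variance of the decline rate at an alpha level of .05". Neither sidedness nor the size of any variance difference is given.
- The result: "A total sample-size of 350 was required for power of .84".
- The conclusion, after planning to recruit 420 and allowing for about 17% attrition: "giving sufficient power to detect the primary effects".

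Under Analysis, both arms share one normative trajectory, a treatment slope is added in the active arm, and the decision rule is: "Statistical significance of the mean of the treatment slope indicates a significant main treatment effect".

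Allocation is 1:1 (Randomisation, allocation, and blinding). The hypothesis is slower decline in the supplemented arm (Methods/Design).

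**The concern.** The two sections describe different tests. A difference in the variance of decline is not slower decline, and under the Analysis section it does not count as a main treatment effect. Power that partly comes from detecting a variance difference therefore cannot show that the trial is adequately powered for its primary hypothesis. Yet the Power section ends by calling the sample size sufficient for the primary effects.

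The mismatch matters only if the mean-slope test alone has materially lower power. If it does, a reader who takes .84 at face value will treat a non-significant treatment slope in a cognitive domain as stronger evidence against an effect than the design supports.

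**Working it through.** **Inputs.** Slope difference .23 control-slope SD; total N = 350; alpha .05 (Power). 1:1 allocation, so 175 per arm (Randomisation). Test of the mean treatment slope, common trajectory, four equally spaced waves (Analysis).

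**1. Trying to reproduce .84 from the mean effect.** Suppose each participant's true slope were observed without error, slope variances were equal, and slope were uncorrelated with initial status. Then z = .23 × √(350/4) = .23 × 9.354 = 2.151.

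- Two-sided: Φ(2.151 − 1.960) = .576.
- One-sided: Φ(2.151 − 1.645) = .694.
- Using d = .2 directly as the slope difference: .464 two-sided, .589 one-sided.
- Ignoring attrition, two-sided at .23: .654 with 420 and .623 with the 391 participants reported in the Abstract.

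None gives .84.

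**2. Reading 350 as per arm.** z = .23 × √(700/4) = 3.043, so two-sided power is .861. At d = .2 one-sided, power is .842. These come close to the stated figure, but the article says total.

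**3. The wider test.** In a 2-df joint test of mean and variance with error-free slopes and no variance difference, the noncentrality is about (350/4) × .23² = 4.63, giving power .47. Power .84 on 2 df needs a noncentrality of 10.64. With treated-to-control slope variance ratio r, the noncentrality is 175 × [2 ln v − ln r], where v = (1 + r)/2 + .23²/4. Setting this to 10.64 gives r of about 1.49. No such variance effect is stated.

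**4. Adding measurement error (assumed values).** Take a linear growth model with waves at 0, 1, 2 and 3, a common intercept mean, slope variance equal to 20% of initial-status variance (one reading of the bracketed remark) and zero correlation. The standard error of the treatment slope comes from the generalised least squares information matrix. Two-sided power:

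| Residual variance ÷ initial-status variance | Power |
|---|---|
| 0 | .58 |
| .25 | .49 |
| .5 | .44 |
| 1.0 | .37 |

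**5. Adding intercept-slope correlation ρ.** Because both arms share one trajectory, initial status can sharpen the slope comparison. With no measurement error, z becomes 2.151/√(1 − ρ²):

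| \|ρ\| | Two-sided power, error-free |
|---|---|
| 0 | .58 |
| .3 | .62 |
| .5 | .70 |
| .69 | .84 |

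The last row solves √(1 − (2.151/2.954)²) = .685, where 2.954 = 1.960 + .994. With residual variance .25, power is .55, .64 and .79 at ρ = −.3, −.5 and −.7, and .49, .52 and .57 at the positive values.

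**6. What 350 can detect.** Under the assumptions of step 1, the slope difference detectable with two-sided power .84 is 2.954/9.354 = .316, about .32 slope SD. Power .84 for .23 would need 4 × (2.954/.23)², about 660 in total.

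**The case against.** A reader might infer from step 1 that power is at most .58, that at least 42% of real effects of the planned size would be missed, or that 660 participants and .32 SD are strict bounds. The documents do not support that. Those figures assume a two-sided test and no intercept-slope correlation, and the article fixes neither. The hypothesis is directional, and the common-trajectory model lets initial status contribute. One-sided, error-free power reaches about .85 at |ρ| = .6. So .58 is a result under named assumptions, not a ceiling.

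The article also says openly that its power refers to a mean and/or variance difference; it does not label .84 as power for the mean alone. It took its approach from a published power analysis on an artificial dataset, whose variance, correlation and residual settings are not shown here. The authors' own calculation therefore cannot be called wrong. Nor is the effect scale beyond dispute: if d = .2 refers to the true-score SD at the fourth wave and slope variance is 20% of initial-status variance, the slope difference is .2 × √(1 + .2 × 9)/(3 × √.2) = .249 SD, and error-free two-sided power at zero correlation is about .65.

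All of this stands, and it limits how the point may be worded. It does not remove the mismatch. Openly defining power for one test does not justify calling it sufficient for effects judged by another. At a total of 350, each route to .84 needs a strong correlation with near-perfect measurement, a strong correlation with a one-sided test, or a sizeable variance difference. None of these is stated.

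**Conclusion.** The point holds in this form. The stated .84 refers to a mean and/or variance difference, whereas the main effect rests on the mean treatment slope. For that test, the stated .23 slope SD at a total of 350 gives about .58 two-sided or about .69 one-sided, assuming error-free slopes, equal slope variances and no intercept-slope correlation. Measurement error lowers this (about .49 to .37 over the assumed range at zero correlation), and correlation can raise it. On the conventional two-sided reading of step 1, an effect of the planned size would be missed about 42% of the time in each domain (1 − .576), against the 16% that .84 implies.

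Whether .84 reflects an unstated variance effect, an unstated correlation or a per-arm figure reported as a total cannot be settled from the article.

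**What to change.** Keep the sample size and the primary test, and revise the Power section as follows.

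1. State power for the mean-slope test with its assumptions: sidedness, slope and residual variances, and intercept-slope correlation. For example: power is about .58 for a difference of .23 control-slope SD at a total of 350 (two-sided .05, error-free slopes, equal slope variances, no intercept-slope correlation); under the same assumptions the difference detectable with power .84 is about .32 slope SD. Do not write this as an upper limit.
2. Confirm whether 350 is a total or a per-arm figure.
3. Either drop .84, or keep it as power for the mean and/or variance comparison and give the variance effect it assumes.
4. Remove or qualify the closing claim of sufficient power for the primary effects.

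The cost is a few sentences and a short recalculation. No participants are added and the analysis does not change, but the reported power will probably look less favourable.

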### Data treatment of cognitive indicators

Treatment and analysis of reaction time data was conducted only on trials with correct responses. Unfeasibly long latencies on single trials and latencies less than 200 ms or greater than 3.5 intraindividual standard deviations above the individual's mean on a particular task were set to missing, and individuals' mean latencies then recomputed. Considering the above factors, if a participant had less than 60% of valid trial data on a particular task, their mean reaction time for the task was set to missing. Participants' scores were also set to missing on a particular speed task if their accuracy was less than 70% on that task. For the speed tasks and excepting the inhibition tasks' difference scores, the inverse of mean correct latencies were used, to normalise the distribution [70] and to express performance as a work rate. For all tasks (both speed and accuracy based), total or mean reaction time scores for data for tasks not completed, or not completed according to correct procedure, were considered missing.

### Modifications to cognitive test battery after baseline assessment

Confirmatory factor analyses were planned on the baseline data (N = 391) to assess the relationships between the tasks and constructs and, in particular, to ensure no empirical redundancy between any of the constructs. The cognitive test battery was potentially to be abbreviated for future assessments, on the basis of the outcomes.

CFA was performed separately on the baseline data for the tasks assessed by accuracy and speed of response, respectively, using full information maximum likelihood estimation in AMOS 7, to deal with the small amount of missing data. For the accuracy based tasks, latent variables were specified for Fluid Intelligence, Working Memory, Short-term Memory, Long-term Memory, and Retrieval Fluency, indicated by the respective tasks specified in Appendix 1 under each construct. The latent variable covariances were free to vary and the residual variances of the immediate and delayed versions of the two memory tasks were allowed to covary to account for their shared methods. All loadings were of at least moderate magnitude, significant, and in the expected direction and the model fit the data well (χ^2 ^= 66.42, *df *= 42, *p *= .010; Root Mean Square Error of Approximation (RMSEA) = .039, 90%CI [.019, .056]; Comparative Fit Index (CFI) = .984; Akaike Information Criterion (AIC) = 162.4); however, the covariance matrix among the factors was not positive definite because the correlation between Long-term Memory and Short-term Memory was near unity (r = .975). To examine whether both factors were necessary, a model was specified without Long-term Memory and with the delayed memory tasks loading on Short-term Memory (χ^2 ^= 71.5, *df *= 46, *p *= .009; RMSEA = .038, 90%CI [.019, .054]; CFI = .983; AIC = 159.5). This model fit the data better. Because an independent Long-term Memory factor could not be identified, the indicators of Long-term Memory were deleted and the model re-estimated (χ^2 ^= 53.8, *df *= 29, *p *= .003; RMSEA = .047, 90%CI [.027, .066]; CFI = .979; AIC = 125.8); this model also fit the data well and to abbreviate the test battery the long-term memory indicators, that is, the delayed word recall and delayed face recognition tasks, were dropped from the test battery for future assessment sessions. This final model was taken as the measurement model for the accuracy-based tasks and is depicted in Figure 1.

**Figure 1 F1:**
[figure not shown]
**Measurement Model for the tasks assessing level of cognitive performance**. Final measurement model of the baseline data for the accuracy-based tasks (χ^2 ^= 53.8, *df *= 29, *p *= .003; RMSEA = .047, 90%CI [.027, .066]; CFI = .979; AIC = 125.8). The Face Memory and Word Memory indicators represent the immediate recall/recognition versions. Correlations are represented by double-headed arrows.

For the speed-based tasks, the model specified latent variables for Simple/Choice Reaction Time, Odd-man-out Reaction Time, Inhibition, Speed of Memory Scanning, and Psychomotor Speed, with the indicators for each factor as specified under each construct in Appendix 1. The model fit was acceptable (χ^2 ^= 171.4, *df *= 104, *p *< .001; RMSEA = .041, 90%CI [.030, .051]; CFI = .979; AIC = 303.4) and, except for Inhibition, the indicator loadings were of moderate to high magnitude, in the expected direction, and significant; the loadings of the Inhibition tasks were generally lower but all were significant except Flanker, which was near zero (-.02). The magnitude of the factor correlations ranged from .19 to .70, all were in the direction indicating positive relationships, and none was so high as to imply redundancy of any factor. The Flanker task was deleted and the model re-estimated (χ^2 ^= 155.9, *df *= 89, *p *< .001; RMSEA = .044, 90%CI [.032, .055]; CFI = .979; AIC = 281.947); all coefficients were significant and the fit statistics for this model were similar but the AIC indicated better model fit. Although the loading of Colour Stroop on inhibition was also low (.18), given the more experimental nature of this factor (ie., not an established unitary construct in the literature) only the Flanker task was dropped from the test battery for future assessments. Figure 2 depicts the final speed measurement model.

**Figure 2 F2:**
[figure not shown]
**Measurement Model for the tasks assessing speed of cognitive performance**. Final measurement model of the baseline data for speed tasks (χ^2 ^= 155.9, *df *= 89, *p *< .001; RMSEA = .044, 90%CI [.032, .055]; CFI = .979; AIC = 281.947). Correlations are represented by double-headed arrows. Abbreviations: RT = Reaction Time; MT = Movement Time.

In total, on the basis of the above analyses, three tasks from the initial test battery were dropped from the battery for the subsequent assessments.

## Conclusions

This methodology and protocol paper provides a detailed overview of the design and implementation of a double-blind, randomised, controlled trial assessing the efficacy of a DHA-rich fish-oil supplement on slowing cognitive decline, over 18-months, in cognitively-normal older adults. This is one of the few trials to date to examine the impact of *n*-3 LC PUFA supplementation on cognitive decline in cognitively healthy older adults. Advantages of the current study are the comprehensive assessment of cognitive functioning and the multiple measurement points, which allow for assessment of an intervention effect on a trajectory, rather than effects at a specific time point. The significance for society could be wide-ranging if such an available and inexpensive dietary treatment has the possibility to safely reduce cognitive decline in ageing, given the links between cognitive functioning and the societal and personal burden of dependency and decreased quality of life in older age.

## Abbreviations

AD: Alzheimer's disease; AIC: Akaike Information Criterion; ApoE: Apolipoprotein E; CES-D: Centre for Epidemiology Studies Depression Scale; CFA: confirmatory factor analysis; CFI: Comparative Fit Index; CFQ: Cognitive Failures Questionnaire; CRP: C-reactive protein; DHA: docosahexaenoic acid; EPA: eicosapentaenoic acid; FAME: fatty acid methyl esters; FFQ: food frequency questionnaire; HbA1c: glycated haemoglobin; HDL: high-density lipoprotein; HPLC: high performance liquid chromatography; LDL: low-density lipoprotein; LGCM: latent growth curve modelling; LLFDI: The Late Life Function and Disability Instrument; MDA: malondialdehyde; MMSE: Mini-mental State Examination; *n*-3 LC PUFA: omega-3 long-chain polyunsaturated fatty acid; PRMQ: Prospective and Retrospective Memory Questionnaire; PWI: the Personal Wellbeing Index; RCT: randomised controlled trial; RMSEA: Root Mean Square Error of Approximation; SF36V2: SF-36 version 2; SWLS: Diener's Satisfaction with Life Scale.

## Appendix 1: Cognitive test battery

Parallel versions of each task were presented at each assessment visit unless otherwise specified. The Flanker task and the delayed recall tasks for Face Memory and Word Memory were only presented at the first assessment because these tasks were found not to adequately mark the expected latent construct in confirmatory factor analyses of the baseline results, conducted between assessments 1 and 2.

Tests were administered via paper-and-pencil or computer. The order of presentation of tests is indicated in parentheses following the name of the task below. All computerised task scripts, excepting Inspection Time, were written and/or modified using the software Inquisit (v. 2^©^, Millisecond Software). The Memory Scanning and Inhibition tasks were newly devised.

### Knowledge

Vocabulary (#17). 20 items from forms 1 and 2 of the standard, advanced, and extended range vocabulary tests from ETS Kit of Factor-Referenced Tests [71] comprise this multiple-choice task. A 4-minute time limit was imposed.

### Reasoning

Raven's (Standard Plus) Progressive Matrices (#10) [72]. Stimuli are a three by three array of symbols, with the bottom right hand symbol missing. Participants choose, from options given below the matrix, which symbol logically completes the matrix. Twenty items, selected to maintain progressive difficulty, were administered with a ten-minute time limit. The same version was administered at each assessment.

Letter Sets (#13). This task is from the ETS Kit of Factor-Referenced Tests [71]. Stimuli consist of a series of five, four-letter items, which follow a predetermined alphabetical ordering. The task is to determine the rule or pattern linking four of the items and cross-out the item not fitting the rule. Fifteen items comprised this test, administered with a seven minute time limit. The same version was administered at each assessment.

Everyday Problems Test (#19) [73]. This test is an objective measure of adults' ability to solve problems of daily living, presented as printed material, in seven domains considered critical for independent living. The seven domains, similar to those covered by the Instrumental Activities of Daily Living (IADL [74]), are health (medications), meal preparation/nutrition, phone usage, shopping, financial management, household management, and transportation. Stimulus material is in three formats - directions, charts, and forms - and number of questions is balanced across domains and format. For each item, a stimulus (e.g., prescription medication label, phone fee chart, mail-order form) is presented from which the participant must derive the answer through reasoning, to the accompanying item question. The test at each time point comprised 21 multiple-choice items (selected from the full-test 84-item pool), with a 15 min time limit imposed.

### Retrieval Fluency

Word Endings (#18). This test is derived from the ETS Kit of Factor-Referenced Tests [71]. The task is to write down as many words ending with a specific set of letters (e.g., 'in'). The score is the number of valid words written within 2 minutes.

Retrieval Fluency (#21). This test is derived from the Woodcock-Johnson III Tests of Cognitive Ability [75]. Participants have to write as many words falling within a given category as possible, in two minutes. The score is the number of things written, bar repeats.

### Short-term Memory

Face Memory - immediate recall (#1). This task, derived from Herzmann, Danthiir, Schacht, Sommer, and Wilhelm [76], is computerised. 20 photographic portraits are presented with 1.5 mins to study them. Each trial in the subsequent test period presents one of the studied faces next to a completely new face and the task is to indicate which face was the studied face.

First and Last Names (#11). In this paired associates test, derived from the ETS Kit of Factor-Referenced Tests [71], participants are given 2.5 mins to study a list of 15 first and last name pairs. They are then shown only the last names and allowed 1.5 mins to write down the associated first names.

Word Memory - immediate recall (#2). Word list A from the Rey Auditory Verbal Learning Test [77] was presented via computer at the first assessment and parallel word lists were presented for subsequent sessions. 15 words (nouns) were presented, one at a time, on screen for one sec duration, with an inter-trial interval of one sec. Immediately after presentation of the word-list, participants write down, in any order, as many of the words recalled.

### Long-term memory

Face Memory - delayed recall (#29). Approximately 3.5 hrs after presentation of the initial Face Memory task, participants were tested again on the faces studied in that task. Each trial presents one of the studied faces next to a completely new face. The task is to indicate the face that was studied in the initial study phase of the Face Memory task.

Word Memory - delayed recall (#6). Approximately 30 mins after presentation of the initial Word Memory task, participants write down as many words as they can recollect from the list, in any order.

